#### Exposure School Selection

Our research team is identifying all possible intentional school shooting cases via a comprehensive review of multiple national school shooting databases, including the K-12 School Shooting database, the Everytown for Gun Safety database on gunfire on school grounds, and the Washington Post database on school shootings, to identify all schools that have experienced intentional gunfire on campus during school hours [51]. These data document all incidents in which a gun is fired or a bullet hits school property for any reason, regardless of the number of victims, time, or day of the week. Our research team is then coding this list of incidents to identify cases that meet the criteria for intentional school shooting at a secondary (ie, middle or high school level) public school—all cases of intentional gunfire on school property, occurring during school hours (including 1 hour before official school activities begin and 1 hour after all official school activities end), beginning January 1, 2015—to ensure we have enough schools in our sampling frame that meet our aforementioned criteria. We are excluding accidental discharges and attempted suicides where no other person was targeted or shot. We are also excluding any incidents taking place on a school bus and on school property that are noncontiguous with the school’s primary campus. Furthermore, we are cross-referencing our list of incidents with other publicly available data sources [40] to ensure that no incidents meeting our criteria are missed. Two members of our research team are then independently coding this list of incidents to identify the cases that meet our proposed study’s criteria for “intentional school shooting”; a third member of our study team is reviewing any potential discrepancies in coding efforts. The final list of exposure schools will then be divided into 2 based on recentness, that is, schools where the incident happened between January 1, 2015, and December 31, 2021, and schools where the incident happened between January 1, 2022, to December 31, 2023. In total, 3 schools will be randomly selected from each list. In case a school declines to participate, we will move to the next randomly selected school. Nonexposure schools will be matched to the final exposure schools. In case a school declines to participate, we will move to the next randomly selected school.

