#### Students

Within each participating school, all students between grades 6 to 12 are eligible for and invited to participate in this study. To encourage study participation, we are implementing reasonable incentives for participants, keeping the survey as brief as possible, communicating study expectations clearly and consistently, engaging thoughtfully with each school’s leadership team during the recruitment process, and using other best practices [56,57]. Accounting for attrition and individuals choosing not to participate, we expect a 15% to 20% response rate (which is consistent with other research that has involved collecting survey data directly from students, teachers, and principals) [58,59], and therefore, anticipate sampling between 1000 to 1200 students across the 12 participating schools.

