### Data Analysis Plan

The data collected from the students, teachers, and principals across all 12 participating schools will be analyzed and will fully respond to each of the research questions. Descriptive statistics will be calculated to summarize student and teacher participant characteristics within each school and also describe each school’s safety and security strategies. Analyses of covariance will subsequently be used to identify potential significant differences in the prevalence of mental health and well-being, perceptions of school safety, educational outcomes, and ACEs among students in schools that have more recently experienced an intentional school shooting, schools that have experienced an intentional school shooting less recently, and schools that have never experienced a shooting, while controlling for key covariates.

ANOVA will also be used to identify potential significant differences in the prevalence of mental health and perceptions of school safety among teachers in schools that have more recently experienced an intentional school shooting, schools that have experienced an intentional school shooting less recently, and schools that have never experienced an intentional school shooting. We used G^*^Power (version 3.1; Heinrich Heine University Düsseldorf) to run power analyses in anticipation of our proposed analyses, assuming an α level of .05 and a power of 0.80. In the case of our proposed student analyses, a very small minimum effect size will need to be detected to meet our power requirements and given our anticipated minimum sample size (exposure schools: N=500-600, nonexposure schools: N=500-600). In the case of our teacher analyses, a medium effect size will need to be detected and given our anticipated minimum sample size (exposure schools: N=30-60, nonexposure schools: N=30-60). On the basis of the average enrollment across secondary public schools in the United States, we should be able to reach the minimum sample size from 12 schools.

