Multiple regression analyses will then be used to determine if the strength of the association between school safety interventions and mental health outcomes differs among students and school staff in schools with varying levels of trauma exposure. Mediated moderation analyses will evaluate the role of ACEs on the relationships between exposure to an intentional school shooting, exposure to school safety strategies, and student outcomes (ie, mental health and well-being, perceptions of school safety, and educational outcomes) [78]. Again, power analyses revealed that for our student-level analyses and given an α level of .05 and a power of 0.80, a small effect size will need to be detected to meet our power and sample size requirements. In the case of our proposed teacher analyses, a medium effect size will need to be detected. It should be noted that these values reflect conservative estimates with regard to student and staff recruitment. Thus, we are confident that we will achieve reasonable power to fully answer all of our questions and achieve the specific aims of the study.

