### Potential Study Challenges, Limitations, and Strategies to Address Them

We acknowledge the potential challenges this study presents, and we have identified approaches to mitigate specific concerns that may arise in the implementation of the study. The primary challenge is that this study requires voluntary participation of 12 schools, their students, and staff. As noted earlier and to encourage participation, every effort is being made to minimize the time burden associated with participation in this study, prioritize confidentiality of data, and create an inclusive study environment by ensuring that all participants have regular opportunities to ask questions and express concerns throughout the study process. We will also be providing incentives to all participating schools to recognize their time spent on this study.

Other potential risks include emotional responses that may emerge during the data collection process. It is important to underscore that great care will be taken to ensure that the proposed data collection effort takes place in a manner that is comfortable and safe for all participants. It should be noted that our study will not be collecting data on self-harm or suicidality. In addition, the representativeness of our school sample may pose to be a limitation. Indeed, there is such variation in school size, urbanicity, variation by state, and budget, that the schools themselves may not be sufficiently representative of all possible schools meeting our criteria. However, as noted earlier, our sample has sufficient power and we have ensured representation to the best of our ability across geographic regions. Finally, there is the possibility of missing survey data; however, we will be using multiple data sources where possible and multiple imputation methods will be used to address the problem of missing data during the data analysis process.

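### The student power claim counts students as independent, although shooting exposure and safety strategies vary only between 12 schools

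*Protocol article*

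**What the plan says.** Schools are selected by exposure. For the two recency lists, "In total, 3 schools will be randomly selected from each list" (Exposure School Selection), and 6 never-exposed schools are matched on state, urbanicity and school level (Study Design). The safety-strategy score is one sum per school (School Safety and Security). The authors "anticipate sampling between 1000 to 1200 students across the 12 participating schools" (Students).

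The Data Analysis Plan names these tests:
- Students, three school groups: "Analyses of covariance will subsequently be used to identify potential significant differences in the prevalence of mental health and well-being" and the other student outcomes.
- Teachers, the same three groups: ANOVA.
- Safety strategies: "Multiple regression analyses will then be used to determine if the strength of the association between school safety interventions and mental health outcomes differs" by level of exposure.

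Power was computed in G*Power, "assuming an α level of .05 and a power of 0.80", from head counts ("exposure schools: N=500-600, nonexposure schools: N=500-600"). The result is given in words only: "a very small minimum effect size will need to be detected to meet our power requirements and given our anticipated minimum sample size". For the student regression and moderation analyses the word is small, and for teachers it is medium. The limitations section then answers a worry about representativeness partly by stating that "our sample has sufficient power".

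Under Independent Covariates the article also mentions conditional logistic regression and propensity score methods. The article nowhere mentions an ICC, a design effect or a school term.

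**The concern.** When an explanatory variable is constant within a school, extra students sharpen the estimate of that school's mean but add no further schools. The comparison of exposed with never-exposed schools has 12 school means and, unpaired, 10 degrees of freedom, not about 1,000. A power calculation on head counts therefore promises more than the design can give. A student-level test without a school term can also report an ordinary difference between schools as an effect of shootings or of safety measures. This matters because the Conclusions intend the results to inform schools' prevention practices and the allocation of mental health resources.

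**Working it through.** **Inputs.** From the article: two-group α .05 and power 0.80; 500-600 students per side; 12 schools (3/3/6); 30-60 teachers per side. Derived: m = 1000/12 ≈ 83.3 to 1200/12 = 100 students per school. Assumed: two-sided tests, schools of equal size, outcomes on a standardised scale, and ICC ρ = 0.005, 0.01, 0.02 or 0.05.

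**1. The plan's own figure.** With independent students, a two-sample noncentral t calculation gives d = 0.177 at 500 v 500 and 0.162 at 600 v 600. Both lie below the conventional small effect of 0.2, so the plan's wording is reproduced under independence.

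**2. Allowing for schools (m = 83.3).**
- Variance of a school mean: v = ρ + (1 − ρ)/m.
- SE of exposed minus never, 6 v 6 schools: √(2v/6).
- Detectable d = 3.11 × SE, where 3.11 is the noncentrality needed for 80% power on 10 df.
- Example at ρ = 0.01: v = 0.01 + 0.99/83.3 = 0.0219; SE = 0.0854; d = 3.11 × 0.0854 = 0.27.
- Design effect: DE = 1 + 82.3ρ.
- Type I error of a student test that ignores school: 2[1 − Φ(1.96/√DE)] for two groups, and approximately 0.05^(1/DE) for three.

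| ICC | DE | Detectable d, 6 v 6 | Power at d 0.177 | Type I, two groups | Type I, three groups |
|---|---|---|---|---|---|
| 0.005 | 1.41 | 0.23 | 57% | 10% | 12% |
| 0.01 | 1.82 | 0.27 | 47% | 15% | 19% |
| 0.02 | 2.65 | 0.32 | 34% | 23% | 32% |
| 0.05 | 5.12 | 0.45 | 20% | 39% | 56% |

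Simulation (20,000 runs, 83 students per school) agrees: 10%, 14%, 23% and 38% for two groups, and 12%, 19%, 33% and 55% for three. The two-group design effect also applies to a regression slope on a school-level safety score, because that score is constant within a school.

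**3. More students do not restore the claim.** As m grows, detectable d cannot fall below about 2.80 × √(ρ/3), even with normal in place of t quantiles. That is 0.16 at ρ = 0.01 and 0.36 at ρ = 0.05.

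**4. Recency, and the matched pairs.** The power figures cover two groups only. For ρ = 0.01, 0.02 and 0.05, if matching removes no variance:

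| Contrast | SE | df | Noncentrality | Detectable d |
|---|---|---|---|---|
| Exposed v never, unpaired | √(2v/6) | 10 | 3.11 | 0.27, 0.32, 0.45 |
| Exposed v never, pair fixed | √(2v/6) | 5 | 3.51 | 0.30, 0.36, 0.50 |
| Recent v less recent, unpaired | √(2v/3) | 9 | 3.15 | 0.38, 0.46, 0.64 |
| Recent v less recent, pair fixed | √(4v/3) | 4 | 3.76 | 0.64, 0.77, 1.08 |

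The last row is larger because recent and less recent schools lie in different pairs. The contrast becomes a difference between two sets of within-pair differences.

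**5. Teachers.** With 5-10 teachers per school and ρ = 0.05, the two-group type I error is about 7-10%, and simulation gives 8-13% for three groups.

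**The case against.** Four points can be made for the plan.

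- **No ICC is given, and matching and covariates may leave a small one.** This stands as a limit on size. A reader might infer that false-positive rates are several times 5% as a matter of fact. The article does not support that: at ICC 0.005 the two-group rate is about 10%, and larger multiples need a residual ICC of about 0.01 or more.
- **Conditional logistic regression and propensity scores are mentioned.** So it would be wrong to say that the plan ignores matching. These methods deal with covariates and matched sets, not with correlation within a school. Inside a pair, each school's own effect remains confounded with exposure. A simulated matched-pair test that ignored school gave about 39-43% type I error at ICC 0.05, much like the unmatched test.
- **A full analysis plan may fit multilevel models under the labels ANCOVA and regression.** That is possible, and it makes the power statement the firmer target. A later model could control the type I error, but it could not make the head-count power claim true.
- **Not every analysis is affected alike.** This also stands. ACE history and presence at the incident vary between students in one school, and teacher clusters are small. A reader might infer that every power statement in the article fails to the same degree; that would be too broad. The article's description of its values as conservative refers only to recruitment numbers.

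**Conclusion.** The point holds for the school-level questions, that is exposure, recency and safety strategies in students. The very small detectable effect rests on independence of students within schools. For exposed v never-exposed schools, a realistic value is d of about 0.23-0.45 unpaired over ICC 0.005-0.05. At the plan's implied effect of 0.177, power is about 57% down to 20%, not 80%. If the named student tests are run without a school term, type I error is about 10-39% for two groups and 12-56% for three over the same range. All these sizes depend on the assumed ICC, on about 83 students per school and on equal school sizes. The direction does not depend on the exact ICC: any positive within-school correlation raises the detectable effect, and even at ICC 0 a test on 10 school-level df needs d of 0.18-0.20.

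**What to change.** 1. For the exposure, recency and safety-strategy questions, fit models with a random intercept for school and small-sample df (Satterthwaite or Kenward-Roger). Add a school-level analysis as a check. If that check is a permutation test, note its coarseness: with 6 pairs the smallest two-sided p is 2/64 = 0.031, and relabelling 3 v 3 schools gives at best 2/20 = 0.10.
2. State whether matched pair enters the model, since this changes the df and the recency contrast.
3. Restate the detectable effect for the model chosen, with its ICC assumption, taking the matching row of the second table in the working. Give teachers and within-school contrasts their own statements.
4. Remove the very small claim from the Data Analysis Plan and the sufficient-power claim from the limitations section. Qualify the expressed confidence that power will be reasonable for all questions.

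**Cost.** Revised analysis wording and a new power paragraph. No new data are needed, and as published only 3 schools had been surveyed by May 2024. The price is wider confidence intervals and a less favourable stated effect size.

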#### Teachers

Within each participating school, all teachers are eligible for and invited to participate in this study. Multiple efforts are being made to maximize participant recruitment and retention. We anticipate a minimum of 60 teachers and upward of 120 teachers (5-10 teachers per school, on average) to participate in this proposed study.

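### The 'medium' detectable effect stated for the teacher ANOVA does not follow from 60 to 120 teachers: the planned three-group test has 80% power for f = 0.41 at 60 and f = 0.29 at 120

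*Protocol article*

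**What the plan says.** - **Planned test.** Data Analysis Plan: "ANOVA will also be used to identify potential significant differences in the prevalence of mental health and perceptions of school safety among teachers". The sentence goes on to name three groups of schools: a more recent shooting, a less recent one, and none.
- **Design values.** The power analyses were run in G*Power 3.1, "assuming an α level of .05 and a power of 0.80".
- **Stated result for teachers.** "In the case of our teacher analyses, a medium effect size will need to be detected and given our anticipated minimum sample size". The sample is then given in two groups, not three: "exposure schools: N=30-60, nonexposure schools: N=30-60". No numeric effect size appears.
- **Expected sample.** The Teachers section under Sampling Frame says "We anticipate a minimum of 60 teachers and upward of 120 teachers (5-10 teachers per school, on average". Over 12 schools this is the same 60 to 120.
- **Statements that rest on this.** The last paragraph of Data Analysis Plan repeats 'medium' for the teacher regressions and expresses confidence that power is adequate for every question. The section on potential challenges and limitations then cites sufficient power as an answer to limited representativeness.

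**The concern.** Significance level, power, number of groups and sample size are all given, so the detectable effect can be recomputed. Two things look wrong. First, the test has three groups but the sample is described for two, so the power calculation and the planned analysis may not be the same. Second, 60 teachers is few for a medium effect under either layout.

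Staff appear in the second and third research questions, so the teacher results will be read in their own right. If a non-significant teacher ANOVA is interpreted against the stated 'medium', readers may take it as evidence against a medium difference. At the lower end of expected recruitment the planned test would miss a true f = 0.25 about 63% of the time (100% - 37%).

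**Working it through.** **Inputs from the article**
- Significance level 0.05 and power 0.80 (Data Analysis Plan).
- Three groups, k = 3 (Data Analysis Plan). Exposure School Selection draws 3 schools from each recency list, and there are 6 nonexposure schools, so the groups are roughly 1:1:2. At a given f, power depends only on total N.
- Total N = 60 (30 + 30) to 120 (60 + 60).

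**Assumption.** 'Medium' means f = 0.25 or d = 0.5, and 'large' means f = 0.40 or d = 0.8. These are conventional benchmarks; the article gives no number.

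**Formula, one-way ANOVA** (the noncentral F calculation that G*Power uses): noncentrality λ = f² × N, degrees of freedom k - 1 and N - k. Power is the probability that a noncentral F exceeds the 5% critical value.

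**Step 1. Can 'medium' be reproduced for the planned three-group test?**

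| N | df | Critical F | λ at f = 0.25 | Power at f = 0.25 | Power at f = 0.40 | f detectable at 80% |
|---|---|---|---|---|---|---|
| 60 | 2, 57 | 3.16 | 0.0625 × 60 = 3.75 | 37.4% | 77.6% | 0.41 |
| 120 | 2, 117 | 3.07 | 0.0625 × 120 = 7.50 | 67.6% | 97.9% | 0.29 |

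Check on the last column: 80% power needs λ of about 10.2 at N = 60 (0.4115² × 60) and about 9.9 at N = 120 (0.287² × 120).

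The smallest N with 80% power for f = 0.25 is 158, where λ = 0.0625 × 158 = 9.9, or 159 in equal groups. That is 158 / 60 = 2.6 times the stated minimum. The stated figure is not reproduced.

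**Step 2. Can it be reproduced as a two-group comparison?** Noncentrality of the t statistic is d × √(n/2) with n per group, two-sided.

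| n per group | Noncentrality at d = 0.5 | Power at d = 0.5 | d detectable at 80% |
|---|---|---|---|
| 30 | 0.5 × √15 = 1.94 | 47.8% | 0.74 |
| 60 | 0.5 × √30 = 2.74 | 77.5% | 0.52 |

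A medium effect needs 64 per group, 128 in total. The lower end fails clearly; the upper end falls short by 2.5 percentage points.

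**Step 3. Can it be reproduced one-sided?** Power for d = 0.5 is 60.6% at 30 per group and 86.0% at 60 per group (51 per group needed). Only the upper end passes, and a one-sided two-group test is not the planned ANOVA.

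**Step 4. The separate regression statement.** With f² = 0.15 as medium and N = 60, power for one tested coefficient is 83.9% and the detectable f² is 0.14. Here 'medium' is reproduced.

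**Step 5. Clustering, as sensitivity only.** The figures above treat teachers as independent. The article gives no intraclass correlation (ICC), so this is an assumed range. With m = N/12 teachers per school and effective N = N / (1 + (m - 1) × ICC), an ICC of 0.01 to 0.10 moves the three-group detectable f to 0.42 to 0.49 at N = 60 and to 0.30 to 0.40 at N = 120.

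**The case against.** **'Medium' may be a band.** With no number given, it could cover everything from medium up to large. On that reading d = 0.74 and d = 0.52, and f = 0.29 at 120 teachers, all count as medium. This is the best defence, and it shows that the two-group figures are not far outside ordinary usage. It does not rescue the sentence. The sentence ties 'medium' to the anticipated minimum sample, and at 60 teachers the planned three-group test needs f = 0.41, past even the large benchmark of 0.40, though only just.

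**The power analysis may have used two groups.** The split of the sample suggests so. Then the calculation does not match the test it is meant to support, and a benchmark medium effect is still not reached at 30 per group.

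**The article condenses a fuller power analysis.** That would excuse leaving the number out. It does not excuse a stated result that the article's own inputs contradict.

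**Points on the other side that stand in full**
- A reader might infer that the teacher analyses can detect only large effects. This is not supported at 120 teachers under either layout, nor for two groups at 60, where d = 0.74 is below 0.8.
- A reader might take the remark that "these values reflect conservative estimates with regard to student and staff recruitment" as a claim about effect size that errs in the wrong direction. It is about expected headcount, and nothing in the article shows that 5 to 10 teachers per school is optimistic.
- A reader might treat 120 as a ceiling. The text says "We anticipate a minimum of 60 teachers and upward of 120 teachers", every teacher is invited, and no cap is set.
- A reader might extend the problem to the teacher regressions. That statement holds for a single tested coefficient, and the article does not say how many coefficients are tested together.

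**Conclusion.** The statement is wrong as written, for the teacher ANOVA only. On the conventional benchmarks, no ANOVA or t-test version tried reaches 80% power for a medium effect at the stated minimum of 60 teachers. At 120 the planned test misses it by about 12 percentage points (80% - 67.6%), while a two-group comparison nearly reaches it.

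The conclusion depends on reading 'medium' as f = 0.25 or d = 0.5. It does not depend on clustering, whose size would have to be assumed and which would only widen the gap. Nor is it a reason to change which teacher contrast comes first; that would be a design preference, not the correction of a figure. The general expressions of confidence in power cannot rest on this calculation as far as the teacher ANOVA is concerned.

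**What to change.** 1. In Data Analysis Plan, replace the teacher sentence with something like: *With 60 to 120 teachers, the three-group ANOVA has 80% power at a significance level of .05 for f = 0.41 to 0.29, before any allowance for clustering of teachers within schools.* If a two-group calculation was run, say so and give its figures (d = 0.74 to 0.52) beside those for the planned test.
2. Limit the confidence statement that closes Data Analysis Plan, and the reference to sufficient power in the limitations section, so that neither covers medium effects in the teacher ANOVA.
3. Leave the remark on conservative recruitment estimates, the regression statement and the order of the teacher contrasts as they are.

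The cost is one rewritten paragraph and a qualifying phrase in the limitations section. No extra participants or data are needed; the published figure becomes less favourable. The change should be made before any non-significant teacher result is interpreted.
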